### Co-active coaching plus health education intervention

Participants in the intervention group receive the same six health education sessions described above, plus Co-Active coaching. Parent participants create a schedule with their coach to receive nine, 20-min, one-on-one, telephone-based coaching sessions (3/month for 3 months) focusing on the agenda of the parent’s choosing. Parent participants are matched with a CPCC and together, they create a schedule to engage in nine, 20-min, one-on-one telephone-based coaching sessions (3/month for 3 months). Thereafter, the participant calls the CPCC at the pre-arranged time and at the start of the conversation the client is responsible for identifying the agenda on which they want to focus during that session. The coach has been asked to use only their CPCC skills, which include but are not limited to asking genuinely curious open-ended questions, reflecting back what the participant says, acknowledging the experience that the participant shares, and championing their progress. For a full review of the Co-active coaching approach, see Co-Active Coaching: Changing Business, Transforming Lives [36].

### Measures

At baseline, the parent participant is asked to complete demographic information forms on behalf of themself and their child. Both groups complete the same assessments at each follow-up period and these consist of BMI (height and weight), waist circumference, step count, dietary intake, standardized and previously validated measures (a detailed list is included below), and open-ended questions to glean parents’ perceptions of how the intervention is impacting them and their child (any domain the parent chooses to discuss).

### Primary outcome measures

#### 7-day step count

Yamax Digi-Walker SW-650 pedometers are provided to participants (for both parent and child), as this model is used frequently in research [59, 60]. The Digi-Walker SW-650 records steps, calculates distance travelled based on individual stride length, and has a stopwatch. For the purpose of this study, only step-count data are recorded. Participants are asked to wear the pedometer for all waking hours except when swimming or bathing, and to reset it to zero each morning, over the course of one week (7 days; [59]) at all measurement time points.

#### 24-multi-pass recall

This tool is typically conducted via in-person or telephone interview; however, for the purposes of this study, dietary intake data is being conducted online. Arab and colleagues [61] tested the validity of web-based, 24-h recall within two ethnicities. When testing attenuation factors (λ; the degree to which correlations between dietary intake and true intake were underestimated or overestimated because of random error in reporting), the researchers found that the entire cohort reported high (λ = 0.28) attenuation factors with web-based recall. Additionally, the rate of underreporting of more than 30% of calories was low – 25 and 34%, for African Americans and Caucasians, respectively; [61]).

#### International physical activity questionnaire (IPAQ)

The IPAQ is a self-reported measure of PA that has been validated, and deemed acceptable for monitoring levels of physical activity, among 18–65 year olds in diverse settings [62]. Participants are asked how many days per week, and how many minutes per day they walked and engaged in moderate-intensity and vigorous-intensity activities during the past week [62]. Sedentary behaviours are assessed by asking about sedentary time accumulated from traveling, at work, watching television, and using a computer at home and at leisure; [62]). Test-retest reliability data for the long IPAQ questionnaire show Spearman correlation coefficients around 0.80, indicating very good repeatability, and criterion validity correlations ranged from 0.14 to 0.53, with a median of 0.30 [62].

#### Treatment self-regulation questionnaire (TSRQ)

The TSRQ [63] is used to determine why participants engage or would engage in healthy behaviour (i.e., their motivations). Responses are ranked on a 7-point Likert scale ranging from not at all true (1) to very true (7). Levesque and colleagues [64] used exploratory factor analysis (EFA) and confirmatory factor analysis (CFA) to test the validity of the 15-item TSRQ factorial structure. The researchers hypothesized that a 4-factor structure would emerge with: autonomous (i.e., self-determined) motivation, introjection (i.e., behaviours that have been partially taken in by the person, and are performed to avoid feeling guilty or ego involved), external (i.e., behaviour that is performed in order to obtain a reward or to avoid negative consequences), and amotivation (i.e., absence of motivation) factors [64]. The TSRQ has been validated previously with acceptable internal consistency (α > .73), and established as a useful assessment tool across various settings and for different health behaviours (e.g. tobacco, diet, and exercise; [64]).

#### In-person interviews

In-person, semi-structured interviews, exploring parents’ experiences and perceptions of the program, are conducted at each follow-up point. All interviews are voice-recorded and transcribed verbatim.

### Secondary outcome measures

#### Body mass index (BMI)

Parental height and weight is measured at baseline and each follow-up point to track changes in BMI over time.

#### Multi-dimensional scale of perceived social support (MSPSS)

The MSPSS [65] is a 12-item scale designed to measure perceived adequacy of support from family, friends, and significant others [65]. It uses a 7-point Likert scale, ranging from disagree (1) to very strongly agree (7). When assessing psychometric properties of the scale, Zimet and colleagues [66] found relatively high levels of mean support in the three sample groups they studied (6.01, 5.60, and 5.58), and an internal consistency (Cronbach’s alpha) ranging from α = 0.84 to 0.92 for the overall scale. The researchers also assessed the validity of the family and significant other subscales using multivariate analysis of variance (MANOVA) and found that both scales were significant [66].

#### Rosenberg self-esteem scale (RSE)

The purpose of the 10-item, uni-dimensional RSE [67] is to measure both positive and negative feelings about self-esteem. The RSE is comprised of a Guttman scale, using 4 response categories (strongly disagree, disagree, agree, strongly agree), and is scored on a metric ranging from 0 (poor) to 30 (excellent; [68]). Item convergent validity is generally considered satisfactory if an item correlates r ≥ .40 with its hypothesized scale after correction for overlap; the RSE met this criterion for all items overall and across subgroups [68]. Internal consistency of the scale was α = 0.91 [68].

#### Weight efficacy lifestyle (WEL) questionnaire

The WEL Questionnaire [69] consists of 20-items, which ask participants to rate their confidence about being able to successfully resist the desire to eat, using a 10-point Likert scale ranging from not confident (0) to very confident (9). The internal consistency of the scale ranged from α = 0.70 to 0.90.

#### Self-efficacy for overcoming barriers

These scales assess self-efficacy for performing PA and nutrition behaviours [70]. Self-efficacy for PA is a 12-item measure assessing how confident individuals feel (on a scale of 0–100) when overcoming barriers to being physically active. Participants also completed an 11-item measure to assess how confident individuals feel, on a scale of 0 (not confident at all) to 100 (very confident) when facing barriers to eating a well-balanced diet. Previous research supports the reliability of these scales, with alpha coefficients ranging from 0.73 to 0.95 [47, 49, 70]

#### Eating self-efficacy scale (ESES)

To further assess self-efficacy and eating behaviour, the 25-item ESES [71] is being utilized. Responses are ranked on a 7-point Likert scale ranging from no difficulty controlling eating (1) to most difficulty controlling eating (7). The ESES had a high internal consistency (α = 0.92), and the test-retest reliability over a 7-week period was also acceptable (r = 0.70, *p* < 0.001; [71]).

#### Generalized self-efficacy (GSE) scale

The GSE [72] is a 10-item scale that assesses participants’ coping ability across a wide range of demanding or novel situations [73]. It uses a Likert scale ranging from 1 (not at all true) to 4 (very true). The GSE has been used in a variety of research studies, typically yielding internal consistencies between α = 0.75 to 0.91, and a test-retest reliability (over a half-year period) of r = 0.67 [73]. When tested through an online platform, the GSE had an internal consistency of α = 0.87 (based on *n* = 1314 participants with complete data; [73]).

#### Short-form 36 (SF)-36

The self-administered 36-item SF-36 [74] is used to measure health on eight multi-item dimensions, covering functional status, well-being, and overall evaluation of health [75]. The SF-36 had an internal consistency of α > 0.85, and test-retest reliability was conducted over a two week interval and, for all dimensions, 91–98% of cases lay within the 95% confidence interval constructed for a normal distribution [75].

### Data analysis

SPSS (version 24) will be used to conduct a repeated measures MANCOVA to assess differences within groups, and a two-way ANCOVA to assess differences between groups, where baseline data will be the covariate, with differences analyzed using the post-hoc Least Square Differences method. As socioeconomic status (SES) has an impact on nearly all health issues, including obesity, and understanding its impact in the proposed project is necessary, a general linear model utilizing SES as covariate will be completed. Classification for SES will be based on education and low income cut off scores (LICO) utilizing Statistics Canada’s definition. The semi-structured interview responses from parents, to determine changes in family health behaviours and overall program experiences, will be analyzed in NVivo by two independent researchers. Inductive content analysis (a method in which patterns, themes, and categories emerge from the data, without an existing framework; [76]) will be employed to identify feedback themes. This process involves open coding, in which data is read through several times, and as many headings as necessary are written down to describe all aspects of the content [77]. The headings are then collected on a coding sheet, and categories are grouped and sorted into higher order headings [78, 79]. Data are classified into groups in order to help describe a phenomenon, increase understanding, and generate knowledge [80]. Once categories are decided upon, the two researchers compare headings and come to consensus on final themes, with the support of NVivo software.

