**Methods:**

Using a randomized controlled trial design, the researchers aim to identify the impact of coaching plus education (intervention) compared to education only (control) on parents with overweight/obesity and their children (ages 2.5–10, of any weight). A total of 50 dyads are being recruited and randomly assigned using a 1:1 ratio into the control or intervention group. The control group receive 6 webinar-based education sessions focused on physical activity and nutrition. The intervention group receive the same education sessions and nine, 20-min telephone-based sessions with a certified coach. Coaching and health education sessions are conducted with the parent/guardian of the dyad. This paper provides a detailed methodological account of this program.

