#### Sample size and eligibility criteria

A sample size calculation was conducted using the Horatio Computer Software program [57]. The inclusion of 50 parent-child dyads was deemed sufficient to detect a large effect size (d = 0.8) of a two-level, between groups independent variable, 79% of the time, using a 0.05 alpha level.

To be eligible for this study, parents/guardians must have a BMI of > 25 kg/m^2^, live with their child (aged 2.5–10) for at least 5 days of the week, speak English, and are comfortable using a computer for data collection purposes. Because adolescence spans 10–19 years [58], the research team decided targeting children aged 10 and under for the study described in this paper would be the most impactful. If there are two parents and two children in a family who meet the inclusion criteria, they are permitted to participate as two separate dyads. In the case where two parent-child pairs within the same household are both randomized to receive the intervention, the parents will work with two different coaches.

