#### Data collection

Rolling enrollment has been adopted, making the data collection periods tailored to each individual in the study. Data are being collected at baseline (i.e., one week prior to the start of the intervention); six weeks into the intervention; immediately post-intervention (i.e., three months); and six months post-intervention. All data is being entered electronically at the host university, on a secure server. Consent and other written forms are stored and locked in a secure drawer, in a locked office, at the host university. In order to maintain confidentiality and anonymity, participants are assigned a unique identification code upon registering in the study. Participant files will be kept in storage for up to 5 years after completion of the study. Baseline and follow-up assessments are conducted at the host university or at the participant’s home by the lead researcher and a research assistant. An email link is sent to parent participants asking them to complete the questionnaires, and email and telephone reminders are conducted one and two weeks later if no response is received. If there is no response, it is assumed that the participant has missed the data collection time and contact re-commences at the next follow-up time. If a participant cannot be contacted after three consecutive communication attempts, it is assumed that they are lost-to-follow-up. A grocery store gift card is provided to participants who complete the study. An overview of study measurements and time points can be found in Table 1.

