### Strengths and limitations

In contrast with previous parent-child interventions, to the best of the researchers’ knowledge, this is the first study that will evaluate the impact of Co-Active coaching and/or education on the family unit, via parent and child outcome measures. The use of mixed methods (i.e. using both qualitative and quantitative measures) ensures that the researchers will gain an in-depth understanding of participants’ experiences with both the program and process of developing healthy behaviours. In addition, the randomized controlled trial design, use of a comparison group, and incorporation of several previously validated tools also serve as strengths in this study. Interventions that are based on the foundation of health promotion (i.e. enabling individuals to improve and increase control over their own—and in this case, their family’s—health [81]) have been shown to result in successful behaviour change [35]. This program employs education and coaching, both of which encourage participants to develop skills that will allow them to increase control over their health decisions and environments [82]. Another strength of the study is the selected coaching method in that all CPCCs involved are trained in the same manner; meaning participants in the coaching group are receiving similar strategies to help target their areas of concern [82].

A limitation of this study may be the number of participants who do not complete the program; researchers have reported participants in control conditions of lifestyle interventions are more likely to drop out [82, 83]. To counteract this, and encourage full participation, the researchers remain in contact with participants throughout the study (via email reminders to complete assessments, and in-person follow-ups). A further limitation of this study may be low participation of fathers; a review examining the involvement of fathers in pediatric obesity treatment and prevention programs with parental involvement outlined that, out of 213 included RCTs, only 6% of participants were fathers [84]. The researchers are recruiting parents using many different methods, in hopes of reaching both mothers and fathers.

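### The SPSS repeated-measures MANCOVA named for within-group change drops anyone with a single missing value, although the protocol expects missed rounds and dropout

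*Protocol article*

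**What the plan says.** The Data analysis section of the protocol article assigns two methods to two questions. Change over time within groups gets a repeated-measures model: "SPSS (version 24) will be used to conduct a repeated measures MANCOVA to assess differences within groups". The comparison of arms gets "a two-way ANCOVA to assess differences between groups, where baseline data will be the covariate". The section names neither imputation nor a likelihood-based longitudinal model, and it does not say how many outcomes enter one MANCOVA.

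The Data collection section sets four time points: baseline, six weeks, three months (end of intervention) and six months after the intervention. Someone who does not answer the reminders is kept in the study: "it is assumed that the participant has missed the data collection time and contact re-commences at the next follow-up time". A separate rule defines loss to follow-up. Neither rule comes with an expected rate.

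Strengths and limitations names non-completion as a possible weakness and cites reports that "participants in control conditions of lifestyle interventions are more likely to drop out". The remedy given is continued contact with participants.

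The abstract gives the sample size: "A total of 50 dyads are being recruited and randomly assigned using a 1:1 ratio". The sample size section states that this number detects d = 0.8 "79% of the time, using a 0.05 alpha level" for a between-groups factor, with no allowance for attrition stated.

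**The concern.** A repeated-measures MANCOVA treats each participant's values across visits as one response vector. If any element is missing, the whole vector is unusable and the software deletes the case. This is a property of the method; the documents do not state it.

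Set against the protocol's own expectations, that is a poor match. The follow-up rules go to some trouble to bring back people who missed a round, yet the named analysis would ignore both their later data and their earlier data. Someone who leaves after week six contributes nothing, not even the six-week change. If dropout is higher in the control arm, as the protocol anticipates, the completers also form a more selected group in one arm than in the other.

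At stake is the precision and representativeness of the within-group results in a trial of only 50 dyads.

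**Working it through.** **Inputs from the protocol.** 50 dyads, 1:1, taken as 25 per arm; d = 0.8; alpha 0.05; stated power 79%; four time points, hence three follow-ups.

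**Assumed.** The probability m of a missing value at each follow-up: 5%, 10%, 15%, 20%. Baseline is complete and misses are independent across visits.

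**The plan's own figure.** A two-sided, two-sample t-test with 25 per arm, d = 0.8 and alpha 0.05 has 79.1% power, which agrees with the stated 79%. The figure describes a comparison of arms at full enrolment.

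**Dyads kept, one outcome.**
- Complete at all three follow-ups: 50 × (1 − m)³.
- Seen at any one follow-up: 50 × (1 − m).

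| m | (1 − m)³ | Complete at all visits | Seen at one visit | Excluded by requiring all visits |
|---|---|---|---|---|
| 5% | 0.857 | 42.9 | 47.5 | 14% |
| 10% | 0.729 | 36.5 | 45.0 | 27% |
| 15% | 0.614 | 30.7 | 42.5 | 39% |
| 20% | 0.512 | 25.6 | 40.0 | 49% |

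**Sensitivity to the independence assumption.** If the same people miss every round, the complete set equals the single-visit set (47.5, 45, 42.5, 40) and requiring all visits costs nothing beyond that. The table is therefore the larger-loss case for one outcome.

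**Sensitivity to several instruments.** If k instruments must all be present, each independently missing 5% of the time per follow-up, the complete number is 50 × 0.95^(3k). For k = 4 this is 50 × 0.95^12 = 27.0; for k = 6 it is 50 × 0.95^18 = 19.9.

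**Degrees of freedom, only if outcomes are modelled jointly.** With p scores at four visits there are 3p time contrasts. In a fit pooling both arms the error df are N − 2, so the multivariate time test has N − 2 − 3p + 1 = N − 3p − 1 denominator df and needs N ≥ 3p + 2 complete cases.
- p = 6 (parent and child steps, parent and child diet, IPAQ, TSRQ): at least 20 cases. Denominator df are 31, 17 and 12 at N = 50, 36 and 31.
- p = 9 (the four TSRQ factors scored separately): at least 29 cases.
- p = 15 (adding about one score per secondary instrument): at least 47 cases.

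For p = 6 and a 0.5 SD change in each measure, taken as uncorrelated (noncentrality N × 6 × 0.25), power of the pooled test is about 99.9%, 93% and 79% at N = 50, 36 and 31.

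**The case against.** **The MANCOVA is not the arm comparison.** A reader might infer that power to compare arms falls from 79% to about 65%, 57% or 49% at 10%, 15% or 20% missing per visit. Those values are correct for a t-test on 36.5, 30.7 and 25.6 complete dyads, but the protocol does not carry that set into the arm comparison. It gives that comparison to an ANCOVA which, if run visit by visit, keeps everyone with a baseline value and that visit. This objection stands, and the point is limited to the within-group analysis.

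**Degrees of freedom.** A reader might also infer that the model cannot be computed. That holds for six measures fitted jointly in one arm with 18 or fewer complete cases, but the protocol states neither joint modelling of six measures nor arm-by-arm fitting. In a pooled fit with six measures the test stays computable at every visit-level rate in the table. It fails only with more scores, such as nine at 20% missing (25.6 complete against 29 needed), or if several instruments must be complete together. SPSS's averaged tests under sphericity remain computable in any case, though they delete the same cases. This is a secondary caution.

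**The rates are assumed.** True. The protocol gives none, and clustering of missed rounds in the same people would shrink the loss. The direction does not depend on the rates; the size does.

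**An unseen analysis plan may impute.** It may, and imputing before the MANCOVA would be compatible with the text. The point is therefore not that a missing-data section is absent. It is that the method the article does name fits poorly with the missingness the article itself expects.

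**Conclusion.** The point holds in a limited form. For within-group change, the named method excludes every participant with one missing analysed value, in a trial whose own rules expect intermittent gaps and whose own discussion expects dropout, possibly unequal between arms. For one outcome under independent misses, the loss is 14% of dyads at a 5% miss rate per follow-up and passes a quarter at about 10%. It is smaller if misses cluster in the same people and larger if several instruments must be complete together.

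The conclusion rests on the method's requirement for complete vectors and on the protocol's statements about missed rounds and non-completion. It does not show that the 79% power for comparing arms is wrong, nor that the model will fail to run. The change is worth making because it is cheap and the sample is small.

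**What to change.** In Data analysis, replace the repeated-measures MANCOVA with one likelihood-based linear mixed model per outcome (SPSS MIXED). Fixed effects: arm, visit and arm-by-visit. Within-person covariance: unstructured. Include every participant with any observed visit, and do not require completeness across visits or instruments. Read the within-arm changes from this model, together with the arm contrasts at three months and at six months post-intervention.

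The cost is a few sentences of wording, with the same software, data and number of participants. The model relies on missing values depending only on observed data. That should be stated, but it is a weaker assumption than complete-case analysis makes. Fitting outcomes one at a time also removes the degrees-of-freedom caution.

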### Study purpose

This study will explore the impact of a parent coaching intervention, with parent and child outcomes, on promoting healthy behaviours among the dyad. Specifically, this research aims to identify the impact of a coaching plus health education intervention compared to health education only on: (a) the PA levels of children (ages 2.5–10) and their parents with overweight/obesity; (b) the dietary intake of children and their parents with overweight/obesity; (c) parental motivation to engage in healthy behaviours; and (d) parental perspectives on how the program has impact on their and their child’s nutrition and PA behaviours. These primary outcomes will be measured via in-person parent interviews, parent and child 7-day step count and 24 h dietary intake, and standardized and validated questionnaires. Due to children’s active growth periods, PA and nutrition behaviours can be better predictors of health than anthropometric indicators [54]. Secondary outcomes will be measured by assessing: (a) parental BMI (calculated by measuring weight in kg, over height in m^2^); (b) parents’ overall perception of health; and (c) parents’ psychosocial variables (i.e., social support, self-esteem, and self-efficacy).

The research team hypothesizes that immediately following and at 6 months post-intervention, the coaching plus education group will report higher levels of parent-child PA, greater improvements in parent-child dietary intake choices, greater parental psychosocial benefits, and greater improvements in parents’ BMI values, compared to those who receive education only. The research team predicts that parents from higher socioeconomic status (SES) backgrounds will be impacted more favorably than those from lower SES backgrounds, as researchers have found greater difficulties associated with affecting behaviour change within lower SES environments [20]. It is also hypothesized that male parents and children will have higher PA levels, while female parents and children will have greater dietary intake improvements, and female parents’ psychosocial health will be impacted most positively, given that previous research has found young males tend to be more active than their female counterparts, and obesity affects psychosocial health of women more negatively than men [27].

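### The repeated measures MANCOVA tests change within each arm on complete records, and the between-arm two-way ANCOVA leaves its second factor unnamed; one baseline-adjusted mixed model should be the main analysis

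*Protocol article*

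**What the plan says.** The Data analysis section names SPSS version 24 and plans "a repeated measures MANCOVA to assess differences within groups, and a two-way ANCOVA to assess differences between groups", with baseline as the covariate in the ANCOVA. It does not name the second factor of the two-way ANCOVA.

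The coaching hypotheses in Study purpose compare the arms at two times: "immediately following and at 6 months post-intervention, the coaching plus education group will report higher levels of parent-child PA", relative to education alone. Both arms receive the same six education sessions.

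Data collection sets three assessments after baseline: six weeks, three months (end of intervention) and six months post-intervention. If a parent does not answer the emailed link and its two reminders, "it is assumed that the participant has missed the data collection time and contact re-commences at the next follow-up time". The next sentence but one in sense, on unreachable participants, reads: "If a participant cannot be contacted after three consecutive communication attempts, it is assumed that they are lost-to-follow-up". Strengths and limitations names non-completion as a possible limitation, because "participants in control conditions of lifestyle interventions are more likely to drop out".

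The sample size section gives 79% power with 50 dyads, d = 0.8 and alpha 0.05. It mentions no allowance for loss.

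**The concern.** There are two problems and one side issue.

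- **Within-arm testing.** Change within an arm mixes any coaching effect with the effect of education and with whatever else changes over time, such as season under rolling enrolment. Only the difference between randomised arms isolates coaching. If separate within-arm p-values are read side by side, a significant result in one arm and not in the other can be mistaken for evidence of a difference.
- **An undefined between-arm model.** The repeated measures procedure in the SPSS general linear model uses only records complete on every variable in the model. If time is the unnamed factor and is handled that way, a participant who misses one round is lost from the main comparison as well. If time is entered as an ordinary factor with one row per visit, repeated values from one person are treated as independent and the standard error is too small. If the second factor is something else and the test is run per visit, neither problem arises. The text allows all three readings.
- **Contact rules.** The two rules may classify the same unresponsive parent differently, which affects who supplies later data.

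**Working it through.** **Inputs.** From the article: 50 dyads, 1:1 (25 per arm), d = 0.8, alpha 0.05, stated power 79%, three follow-up visits. Assumed, because the article gives no values: a missed-visit rate m of 5-20%, independent across visits and participants, and a between-visit correlation of 0.5-0.7.

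**1. The stated power.** Two-sample t-test, noncentral t, df = 2n - 2, noncentrality d√(n/2) = 0.8 × √12.5 = 2.83. With n = 25 per arm and two-sided 0.05, power is 0.791. The 79% reproduces, and it needs all 50 dyads.

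**2. Complete records against everyone seen at one visit.** Complete at all three follow-ups: 50(1 - m)³. Seen at one given visit: 50(1 - m). Power uses the same unadjusted t-test.

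| m | Complete dyads | Power | Seen at the visit | Power |
|---|---|---|---|---|
| 5% | 42.9 | 0.73 | 47.5 | 0.77 |
| 10% | 36.5 | 0.65 | 45.0 | 0.75 |
| 15% | 30.7 | 0.57 | 42.5 | 0.72 |
| 20% | 25.6 | 0.49 | 40.0 | 0.69 |

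**3. Three analyses of the last visit, simulated.** 25 per arm, d = 0.8, correlation 0.5, visits missing completely at random, all adjusted for baseline.

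| m (runs) | Complete-case ANCOVA | ANCOVA on all seen at that visit | Mixed model, unstructured covariance |
|---|---|---|---|
| 10% (400) | 0.76 | 0.875 | 0.875 |
| 20% (150) | 0.62 | 0.82 | 0.83 |

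The standard error is 3-4 points at 20%. Type I error was 0.04-0.06 in these runs. The mixed model gains about 11 points (0.875 - 0.76) to 21 points (0.83 - 0.62) over complete cases, and almost nothing over the visit-wise ANCOVA.

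**4. Visits as independent rows.** Three rows per person with residual correlation r inflate the test statistic by √(1 + 2r), so type I error is 2[1 - Φ(1.96/√(1 + 2r))]. Adjusting for baseline under equal correlation ρ among all visits leaves r = ρ/(1 + ρ).

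- ρ = 0.5: r = 0.33, √1.667 = 1.291, 1.96/1.291 = 1.518, error 0.129.
- ρ = 0.7: r = 0.41, √1.824 = 1.350, 1.96/1.350 = 1.451, error 0.147.

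A simulation of 10,000 runs gave 0.133 and 0.150.

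**5. Within-arm tests.** If both arms truly change by the same amount and each within-arm test has power p, exactly one is significant with probability 2p(1 - p): 0.42 at p = 0.3, 0.50 at p = 0.5, 0.32 at p = 0.8. Disagreement between arms is therefore common with no coaching effect at all.

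**6. Contact rules.** One emailed link plus reminders at one and two weeks can be counted as three attempts. On that count, a parent who answers none of them fits both the missed-round rule and the lost-to-follow-up rule.

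**The case against.** The strongest reply is that the right test is already planned. The same sentence that assigns the MANCOVA to within-group change assigns a baseline-adjusted ANCOVA to the comparison of arms. This stands. A reader might infer that the trial has no between-arm analysis, or that it will judge coaching by comparing within-arm p-values. The article says neither, so the disagreement rates in step 5 show why within-arm results cannot answer the hypotheses. They do not describe an error the plan commits.

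Other stronger readings also fail:

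- **That incomplete dyads will be dropped.** The article does not state complete-case analysis. Deletion follows from the named procedure and software, and an analysis plan that is not shown may provide for imputation.
- **That the trial's power falls from 0.75 to 0.65 at 10% missed.** That holds only if the between-arm test runs on complete records. A visit-wise ANCOVA loses nobody for missing another visit and matches the mixed model in step 3.
- **That type I error is 17-21%.** The formula gives 0.166 to 0.206 if 0.5-0.7 is the correlation left after baseline adjustment. For a raw correlation the figure is 13-15%, and either applies only if two-way means arm by time in independent rows. The sex hypotheses in Study purpose make arm by sex a plausible reading too.
- **That the MANCOVA cannot be computed.** This needs many scales in one model, split by arm, with assumed attrition. The article specifies none of these.
- **That the contact rules contradict each other.** One concerns unanswered questionnaires, the other a person who cannot be reached. A parent who is reached by telephone but skips the form meets only the first. The overlap is possible, not proven.

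These points narrow the concern. They do not make within-arm change a randomised comparison, and they do not settle which between-arm model is meant.

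**Conclusion.** The concern holds in limited form. The MANCOVA, as assigned, does not test the coaching hypotheses and, without imputation, uses only complete records in a trial that foresees missed rounds and possibly more control dropout. The between-arm ANCOVA is adequate on one reading, short of data on a second (power 0.73 to 0.49 against 0.77 to 0.69), and anti-conservative on a third (type I error about 13-15%). These sizes rest on the assumed missed-visit rates and correlations above, and the power figures in step 2 take no credit for baseline adjustment.

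The case for a mixed model is not a large power gain over a visit-wise ANCOVA. It is validity when missingness depends on values already observed, including earlier follow-up visits, and one defined arm contrast for each hypothesised time. The contact rules are a secondary point that needs clarification.

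**What to change.** For each outcome, make the main analysis one linear mixed model (SPSS MIXED):

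- follow-up values on arm, visit, arm × visit and baseline;
- unstructured covariance within participant;
- all randomised dyads in their assigned arm, with all observed visits;
- the arm contrast at 3 months and at 6 months post-intervention, each with a 95% confidence interval.

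Label within-arm changes descriptive. Because Sample size and eligibility criteria lets one household enter as two dyads, allow for that clustering, for example with a household random effect. If the team prefers to keep the ANCOVA, it should name the second factor and state that the test is run per visit on everyone seen at that visit.

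Reconcile the two rules in Data collection so that an unresponsive parent falls under only one of them at any round.

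The cost is revised wording and different syntax, with no new measurements. The downside is small: the mixed model relies on missing at random, which the observed data cannot confirm.
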